**Fig. 3 Fig3:**
[figure not shown]
Diagram of the proposed power analysis for the 2 groups in 4 different assessment points using rmANOVA

### Recruitment

Approximately 400 patients with symptomatic KOA visit our clinic annually. A small percentage of patients have end-stage disease and are only amenable to total knee replacement. Most remaining patients initially require conservative measures to control their symptoms, and among those, a respectable percentage has not been able to respond to oral medications, physiotherapy, loss of weight, and injectable therapies. This will be the pool of patients that will participate in our randomized trial. We estimate that we will be able to include 70 patients in the study in 10–12 months.

### Randomization—sequence generation

A total of 70 patients will be included in the study (CRFA:35; CRYO:35) Randomization sequence will be created using Stata 9.0 (StataCorp, College Station, TX) statistical software and will be stratified with a 1:1 allocation ratio using random block sizes of 2, 4, and 6. An investigator not involved in the main study ([name]) will perform the randomization process. These data will be stored on computer and will be available at the day of the intervention.

### Concealment mechanism

For each surgical session including four patients, [name] will seal patient details and the randomized treatment in an opaque envelope that will be given to the coordinated nurse just before the start of the intervention. The patients, relatives, investigators, nurses, and all relevant personnel would be blinded to the indented treatment. The envelope will be opened by the coordinated nurse after the patient is sedated and placed to the radiological table, the knee is properly prepared and the surgeons are sterile and ready to apply the intervention. Both generators for CRFA or CRYO would be available at the interventional radiological department. After opening the envelope, the procedure will be unblinded for all participants.

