### Implementation and blinding

Enrolment of participants will be performed by the main investigators ([name], [name]) at the outpatient office of our department according to the eligibility criteria listed above. The allocation sequence will be created by an investigator not involved in patient care (([name]), and the assignment of participants to interventions by a coordinator nurse at the radiological department who will be responsible for arranging the sessions. The primary investigators ([name], [name], [name]) will be blinded to the intended treatment until the time of intervention; CRFA or CRYO will be applied to each patient after the opening of the sealed opaqued envelope inside the interventional radiological department. Clinical evaluation at 15 days (NPRS, PGIC), 4 weeks (NPRS, PGIC), 12 weeks (NPRS, PGIC, OKS, KOOS), and 24 weeks (NPRS, PGIC, OKS, KOOS) will be performed by an orthopedic resident ([name]) not involved in the initial patient evaluation who will also be blinded to the applied intervention. Data analysists ([name]) and outcome adjudicators will be also blinded during the implementation of the data. Unblinding will be performed in case of severe adverse effects (intense pain, hematoma, nerve damage etc.).

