### Data collection and management

Data will be collected in paper forms at baseline and 2-, 4-, 12-, and 24-weeks post-intervention. Quality assessments and proper training sessions will be conducted to ensure that all information is collected properly. Outcome data include the NPRS, KOOS, OKS, and PGIC, all of which are patient-reported questionnaires. Demographic data, radiographs (downloaded from PACS and saved in JPEG format), and intraoperative pictures of skin marks or videos from the interventions will also be collected. A hard copy folder will be created for each patient, including all paper forms, demographic data, and intervention details. These folders will be kept safe in the hospital office of the primary investigator ([name]) inside a special locker. The other main investigator ([name]) will transfer all the data into an Excel database using the desktop computer at the office of the primary investigator ([name]). Patient identification will be performed using only the national insurance number (11-digit number). Excel forms without patient names will be used for data analysis. Paper forms and computerized data could be assessed only by the two primary investigators. These files will be kept for at least three years after the last enrolled patient for future expansion of the research. We are not expecting participants to discontinue or deviate from the primary intervention. The coordinator nurse will be responsible for contacting them for missing appointments of clinical evaluation, either by phone or email. In case of refusal to attend, we plan to send the questionnaires by mail or make home visits. No other efforts will be made to minimize the loss of follow-up. Missing data from more than one time point will be a reason for dropout from the study.

Data entry, coding, security, storage, assessment of quality and creation of Excel tables will be under the responsibility of the two main investigators. Excel database would be password-protected. Personal information about potential and enrolled participants before, during, and after the trial will be collected to ensure confidentiality (using only the national insurance number as an indicator).

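### Read literally, the protocol unblinds patients once the envelope is opened, and nothing keeps them masked afterwards, although the primary outcome and all other efficacy scores are patient-reported

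*Protocol article*

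**What the plan says.** Concealment mechanism first describes the state before the intervention: "The patients, relatives, investigators, nurses, and all relevant personnel would be blinded to the indented treatment". It then sets the moment of disclosure: "The envelope will be opened by the coordinated nurse after the patient is sedated and placed to the radiological table". The section ends: "After opening the envelope, the procedure will be unblinded for all participants".

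Implementation and blinding describes who is masked later. The primary investigators are masked only up to the intervention. The follow-up resident is described as "not involved in the initial patient evaluation who will also be blinded to the applied intervention". For the analysis stage, the data analysts are masked, and "outcome adjudicators will be also blinded during the implementation of the data". Patients are not on this list. The section adds: "Unblinding will be performed in case of severe adverse effects", without saying whose blind is broken.

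Data collection and management states: "Outcome data include the NPRS, KOOS, OKS, and PGIC, all of which are patient-reported questionnaires". It files the paper forms and the intervention details in one folder per patient, gives data transfer to a main investigator, and limits access: "Paper forms and computerized data could be assessed only by the two primary investigators".

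The title, the opening of Methods and Strengths and limitations all call the trial single-blinded. None of them names the blinded party.

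**The concern.** When the outcome is a self-rating, the patient is the assessor. Masking the person who hands over the form does not mask the person who fills it in. If patients learn their arm on the day of treatment, every later pain score, from 2 to 24 weeks, is given by an unmasked assessor.

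Expectations could differ between the arms. The text under Exclusion criteria describes the CRFA literature as promising up to 12 months and the CRYO data as scarce, and Interim and additional analyses presents CRYO as new and little tested. A difference in expectation would enter the between-arm comparison of NPRS directly, and the planned analyses cannot separate it from a treatment effect. It could also affect requests for pain medication, which the protocol makes a reason for discontinuation, and the interim comparison of clinical outcomes.

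**Working it through.** The plan gives no figure for this point, so there is nothing to reproduce. The check compares the sections.

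**1. Who are the participants in the disputed sentence?** Elsewhere the article mostly uses the word for trial patients: those with bilateral disease (Eligibility criteria), those enrolled and assigned (Implementation and blinding), and those whose personal data are collected (Data collection and management). Where Concealment mechanism means staff, it names investigators, nurses, personnel and surgeons. The natural reading is therefore the patients.

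**2. Does any other sentence keep patients masked after the envelope is opened?**

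| Party | Before the envelope is opened | During follow-up |
|---|---|---|
| Patients | masked | not stated; unblinded on the literal reading |
| Primary investigators | masked | not masked |
| Follow-up resident | not separately stated | masked |
| Data analysts, outcome adjudicators | not separately stated | masked |

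No sentence does.

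**3. Does sedation settle it?** No. The Intervention section specifies conscious sedation, and nothing says the arm is withheld once the patient has recovered.

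**4. Which outcomes are exposed?** All four efficacy scores are patient-reported, so the primary outcome and the KOOS, OKS and PGIC are exposed. Complications are different: they are assessed at each follow-up visit (Outcomes), where the resident's masking helps.

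**5. Data handling.** The people with access to forms and database are the two primary investigators, and the stated blind of the primary investigators ends at the intervention. The folder puts allocation next to the scores. Transcription is therefore not protected by masking either.

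**6. Illustration only: how sensitive a comparison would be.** The bias b is assumed; the document gives no value. Inputs are:
- 35 per arm (Randomization), or 31 per arm, from 62/2 (Sample size);
- SD 2.4, from the cited CRFA versus hyaluronic acid trial at 12 months, and SD 2.8, from the cited 24-month extension of a CRFA trial (both in Discussion);
- a two-sided 5% test of two means at one visit, with no true difference.

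SE = SD × √(2/n). With n = 35 this is 2.4 × √(2/35) = 0.57, and 0.67 with SD 2.8. The rejection probability is 1 − Φ(1.96 − b/SE) + Φ(−1.96 − b/SE).

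| Assumed b (NPRS points) | n = 35, SD 2.4 | n = 35, SD 2.8 | n = 31, SD 2.4 | n = 31, SD 2.8 |
|---|---|---|---|---|
| 0 | 5.0% | 5.0% | 5.0% | 5.0% |
| 0.5 | 14.1% | 11.6% | 13.0% | 10.8% |
| 1.0 | 41.4% | 32.1% | 37.5% | 29.0% |

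The table shows only that a bias well below the protocol's 2-point MCID would matter. It does not show that such a bias will occur.

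**The case against.** The strongest reply is that the sentence may not be about patients. It speaks of the procedure and follows sentences on the nurse, the surgeons and the generators, at a moment when the patient is sedated. The participants could be the people taking part in the room. The rule on unblinding after severe adverse effects also implies that somebody is still masked, and if it refers to patients, it suggests they were meant to stay so. This doubt stands. It does not rescue the plan, because on either reading no sentence keeps patients masked, and staff could not tell from the text whether they may disclose the arm.

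A reader might go further than the document allows in four ways:

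- *That the blinded resident protects nothing.* The masking limits prompting while scores are collected and helps protect the recording of complications, a secondary outcome. Masked analysts and adjudicators protect later steps.
- *That the unblinding rule is pointless if patients already know.* It may concern the resident, the analysts or the adjudicators.
- *That an operator enters the outcome data.* The roles overlap in the text but the names are removed, so this cannot be established. What can be said is that the stated blind of the primary investigators ends at the intervention.
- *That the bias favours a particular arm by a known amount.* Both arms are active, the abstract calls both methods novel, and no size is given.

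It is also fair to object that masking may not fully succeed. Sedation is conscious, motor testing is described only for CRFA, and freeze and thaw phases occur only in CRYO. That limits what the fix can achieve but is no reason to disclose the arm.

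**Conclusion.** The point holds in this form: the literal text unblinds patients when the envelope is opened, no section keeps them masked during follow-up, and the single-blinded label does not say who is blinded. Because the primary outcome is self-rated, the masking that is stated cannot prevent patient-expectation bias in it. The conclusion rests on the wording and on the patient-reported nature of the scores, not on a calculation. The size and direction of any bias cannot be estimated from the document, and the illustrative error rates depend wholly on an assumed bias. The sponsor should correct this: it affects the primary comparison and is cheap to change.

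**What to change.** Replace the last sentence of Concealment mechanism with: *Only the operating team and the coordinator nurse learn the allocation; patients, the follow-up resident and the analysts stay masked until the 24-week visit.* In Implementation and blinding, state whom the unblinding after severe adverse effects concerns, and name the blinded parties wherever the trial is called single-blinded.

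In Data collection and management, file intervention details apart from the outcome forms and have the outcome data entered by someone masked to allocation. At 24 weeks, record each patient's guess of allocation, so that the success of masking can be reported.

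If patients are meant to know their arm, say so plainly and add it to Strengths and limitations, which does not mention it now.

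The cost is protocol wording, staff instruction, separate filing, a masked person for data entry and one question at the last visit. The envelope is already opened after sedation with both generators available, so the session itself need not be rearranged. The downside is that masking may be imperfect, for the reasons given above. The abstract dates the first recruitment to 31 August 2022, so some patients may have been treated under the present wording; what they were told should be recorded.

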### Implementation and blinding

Enrolment of participants will be performed by the main investigators ([name], [name]) at the outpatient office of our department according to the eligibility criteria listed above. The allocation sequence will be created by an investigator not involved in patient care (([name]), and the assignment of participants to interventions by a coordinator nurse at the radiological department who will be responsible for arranging the sessions. The primary investigators ([name], [name], [name]) will be blinded to the intended treatment until the time of intervention; CRFA or CRYO will be applied to each patient after the opening of the sealed opaqued envelope inside the interventional radiological department. Clinical evaluation at 15 days (NPRS, PGIC), 4 weeks (NPRS, PGIC), 12 weeks (NPRS, PGIC, OKS, KOOS), and 24 weeks (NPRS, PGIC, OKS, KOOS) will be performed by an orthopedic resident ([name]) not involved in the initial patient evaluation who will also be blinded to the applied intervention. Data analysists ([name]) and outcome adjudicators will be also blinded during the implementation of the data. Unblinding will be performed in case of severe adverse effects (intense pain, hematoma, nerve damage etc.).

### Data collection and management

Data will be collected in paper forms at baseline and 2-, 4-, 12-, and 24-weeks post-intervention. Quality assessments and proper training sessions will be conducted to ensure that all information is collected properly. Outcome data include the NPRS, KOOS, OKS, and PGIC, all of which are patient-reported questionnaires. Demographic data, radiographs (downloaded from PACS and saved in JPEG format), and intraoperative pictures of skin marks or videos from the interventions will also be collected. A hard copy folder will be created for each patient, including all paper forms, demographic data, and intervention details. These folders will be kept safe in the hospital office of the primary investigator ([name]) inside a special locker. The other main investigator ([name]) will transfer all the data into an Excel database using the desktop computer at the office of the primary investigator ([name]). Patient identification will be performed using only the national insurance number (11-digit number). Excel forms without patient names will be used for data analysis. Paper forms and computerized data could be assessed only by the two primary investigators. These files will be kept for at least three years after the last enrolled patient for future expansion of the research. We are not expecting participants to discontinue or deviate from the primary intervention. The coordinator nurse will be responsible for contacting them for missing appointments of clinical evaluation, either by phone or email. In case of refusal to attend, we plan to send the questionnaires by mail or make home visits. No other efforts will be made to minimize the loss of follow-up. Missing data from more than one time point will be a reason for dropout from the study.

Data entry, coding, security, storage, assessment of quality and creation of Excel tables will be under the responsibility of the two main investigators. Excel database would be password-protected. Personal information about potential and enrolled participants before, during, and after the trial will be collected to ensure confidentiality (using only the national insurance number as an indicator).

### Statistical methods

The sample size and power in the study have been previously described. Another statistical approach for the study is to evaluate all follow-up (post-intervention) measurements separately from the baseline. This may occur in two possible ways: one with the use of an ANCOVA procedure and the other with the use of ANOVA on the difference in the scores (follow-up minus the baseline). As Borm et al. [36] suggested, the ANCOVA approach requires a significantly smaller number of participants, reduced by a multiplicative factor that depends on the correlation estimate between the prior and posterior scores, which is usually high. More specifically, a significance level of 5% along with a power of 80% is achieved with 24–45 patients in total, when the correlation estimates between the a priori and a posteriori score is approximately 80–90%, which is a realistic approach. To sum up with the statistical plan, longitudinal (that is, repeated measures) analysis will be conducted with repeated measures ANOVA. Furthermore, the slopes of the score trajectories (trendlines) will be compared among the two patient groups using 1-way ANOVA. Bivariate comparisons for baseline versus follow-up will be conducted using ANCOVA. 1-way ANOVA will assist in detecting variations in bivariate differences of scores (baseline versus each follow-up) among the two patient groups. Data will be reported as differences between group means (means ± standard deviations, 95% CIs) if normal distributed, otherwise as medians with interquartile ranges. Categorical data will be reported as numbers and proportions. A statistically significant difference of at least two in NPRS scores between groups, will be interpreted as a minimal clinically important difference (MCID). The statistical method of pairwise (available case analysis—ACA) deletion will be used for missing data at only one time point. If more than two time points are missed the list-wise (Complete-case analysis—CCA) deletion method will be used. Statistical analysis will be performed using R language and Rstudio IDE, two well-known open-source products.

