### Sample size

According to the protocol, the patients will be randomly assigned into two groups, and they will all be evaluated (with NPRS) four more times after the baseline assessment (15 days, 4 weeks, 12 weeks, and 24 weeks, post-intervention). The main objective is to examine the possible diversity in NPRS (primary outcome) improvement among patients in different groups. The regular statistical approach to do this is to perform repeated measures ANOVA (rmANOVA), taking as given that all ANOVA assumptions are met (for example, normality of scores). Thus, the statistical power analysis for an rmANOVA procedure is as follows: we, as a priori, assume a number of groups equal to two and a number of measurements (except baseline) equal to four. More specifically, the NPRS is expected to be reduced in the two groups (CRYO and CRFA) at least 30%, relative to baseline assessment. According to Cohen [35], this fact denotes a medium effect size of approximately 0.50. Statistical significance is usually considered at the 5% level, and the power analysis curve for the rmANOVA is shown in Fig. 3. This figure illustrates that approximately 47 patients suffice for an achieved power of 80% using rmANOVA, taking into account a moderate effect size and 62 patients for 90% statistical power. Considering a 10% loss of follow up, we will enroll 70 patients in the study.

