In contrast to cryoneurolysis treatment, where the literature is scarce, the method of radiofrequency ablation for the treatment of symptomatic knee pain in osteoarthritic knees has been well documented in the past. In a cross-sectional survey, McCormick et al. [28] demonstrated a success rate of 35% based on a robust combination of outcome measures, and 19% of the procedures resulted in complete relief of pain at a minimum of six months of follow-up using the CRFA technique. They also demonstrated that 80% or greater relief from diagnostic blocks and a duration of pain of less than five years are associated with high accuracy in predicting treatment success. In their prospective, multicenter, randomized, crossover trial, Davis et al. [18] investigated the analgesic effect of CRFA in patients with knee osteoarthritis 12 months post-intervention and its ability to provide pain relief in patients who experienced unsatisfactory effects of intra-articular steroid injection. They demonstrated that at 12 months, 65% of the original CRFA group had pain reduction ≥ 50%, and the mean overall drop was 4.3 points (p < 0.0001) on the numeric rating scale, while 75% reported ‘improved’ effects. Hunter et al. [45] performed an extended evaluation of the patients enrolled in the study of Davis et al. [18] at 18- and 24-months post-intervention, showing a perceived positive effect with a mean NPRS score of 3.1 ± 2.7, and 3.6 ± 2.8, respectively. In another multicenter, randomized clinical trial, Chen et al. [17] compared the effectiveness of CRFA and a single injection of hyaluronic acid for the treatment of chronic knee pain; at 12-months, 65.2% of participants in the CRFA cohort reported ≥ 50% pain relief from baseline with a mean NPRS of 2.8 ± 2.4 (baseline 6.9 ± 0.8). Participants in the CRFA cohort also showed a 46.2% improvement in the total WOMAC score at the 12-month time point. Carlone et al. [46], in a recent retrospective review of 176 patients who underwent genicular nerve ablation, block, or both, found that 31.8% of the participants failed to respond to the block procedure, mainly due to the associated psychological comorbidities, smoking history, and diabetes. They also demonstrated that of the participants who underwent genicular nerve ablation, 53.7% reported less than 50% pain relief and 46.3% reported pain relief greater than or equal to 50% at the first follow-up visit.

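### The reporting rule drops the between-arm difference and its confidence interval when scores look non-normal, and the 2-point NPRS interpretation is tied to neither summary

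*Protocol article*

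**What the plan says.** Four statements in the protocol article bear on this.

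- **Reporting rule (Statistical methods).** If the data are normal, the report gives the difference between group means with standard deviations and 95% CIs. The condition reads "if normal distributed, otherwise as medians with interquartile ranges".
- **Interpretation rule (Statistical methods).** "A statistically significant difference of at least two in NPRS scores between groups" is to be read as a minimal clinically important difference. The text does not say whether the difference is one of means or of medians, or which model supplies it.
- **Tests (Statistical methods).** "longitudinal (that is, repeated measures) analysis will be conducted with repeated measures ANOVA". ANCOVA and 1-way ANOVA on change from baseline are planned for individual follow-ups. All three compare means, and none is made conditional on the distribution.
- **Normality (Sample size).** The power analysis proceeds "taking as given that all ANOVA assumptions are met (for example, normality of scores", so the design section assumes what the reporting rule leaves open.

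**The concern.** The first branch of the reporting rule is the treatment effect itself: a between-arm difference with its interval. The second is a pair of descriptive summaries. If the rule is followed as written and normality fails, the primary result loses its effect estimate and CI, while the p-value still comes from a comparison of means. A reader could not judge the size of the effect from that combination.

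The interpretation rule then needs a difference of at least 2 points, and the plan does not say where that number comes from. On a short integer scale, mean and median contrasts can fall on opposite sides of 2 in the same data, so the reading can depend on which summary is used. Follow-up NPRS after ablation tends to sit near the floor of the scale, so the non-normal branch is a realistic outcome.

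**Working it through.** **1. Numbers analysed.** The Sample size section asks for 62 patients for 90% power, allows 10% loss and enrols 70. Check: 62 / 0.9 = 68.9, so 69, close to 70. After 10% loss, 70 × 0.9 = 63, or 31–32 per arm. The runs below use 32 per arm unless stated.

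**2. Distance from the floor.** The Discussion cites three follow-up NPRS results after CRFA. A trial against hyaluronic acid gives, at 12 months, "mean NPRS of 2.8 ± 2.4 (baseline 6.9 ± 0.8"; an extension study gives 3.1 ± 2.7 at 18 months and 3.6 ± 2.8 at 24 months. Mean / SD: 2.8 / 2.4 = 1.17; 3.1 / 2.7 = 1.15; 3.6 / 2.8 = 1.29. All lie within about 1.3 SD of zero.

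**3. Simulation.** Assumptions, none of them stated in the plan:
- score = a normal draw, rounded and clipped to 0–10, with the other arm shifted up by the true shift (nominal, before clipping);
- the switch fires if Shapiro-Wilk on raw follow-up scores gives p < 0.05 in either arm;
- significance by t test at 5%.

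The setting 4.5 ± 2.4 is an assumed milder case, not a cited one.

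| Mean ± SD, lower arm | At least one arm non-normal (shift 1.5) | Significant + switch + mean and median disagree on 2 points (shifts 1.5–2.0) |
|---|---|---|
| 2.8 ± 2.4 | 72% | 20–21% |
| 3.6 ± 2.8 | about 50% | 11–14% |
| 4.5 ± 2.4 (assumed) | about 30% | 8–11% |

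**4. How far the summary matters, at 2.8 ± 2.4.** Mean and median contrasts fall on different sides of 2 in 28–30% of trials at shifts of 1.5–2.0. A result that is significant and at least 2 points occurs in:
- 14% of trials by means against 38% by medians (shift 1.5);
- 42% against 67% (shift 2.0).

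**5. Sensitivity to what is checked.** With baseline 6.9 ± 0.8, assumed independent of follow-up, and a shift of 1.5, at least one arm is rejected in 72% of trials on raw scores and 38% on change scores. Pooled change-score residuals are rejected in 23%.

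**6. Sensitivity to shape and number.** With 35 per arm and the clipped normal, the switch fires in 76–93% of runs over shifts of 0–2.5, and the contrasts disagree in 37% (shift 1.5) and 34% (shift 2.0). With a beta shape the switch fires in 98–100%, with disagreement of 49% and 36%. Part of the rise in disagreement arises because the median of an odd number of integer scores is always a whole number.

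**7. What a fixed mean difference would give.** The CI half-width is t × SD × √(2/n). With SD 2.4: 1.995 × 2.4 × √(2/35) = 1.14 points at 35 per arm, and 2.000 × 2.4 × √(2/31) = 1.22 at 31 per arm. Baseline adjustment should narrow this.

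**The case against.** The sentence is about reporting. It is followed by a similar convention for categorical data, and showing means if normal and medians otherwise is widespread practice. A reader might infer that the analysis or the estimand itself switches. The text does not say so: the tests are named without condition, no rank test appears, and a mean difference with CI can be taken from the ANCOVA or ANOVA whatever the distribution. That stands. What remains is that the written rule would not show that estimate in the non-normal case, and that the 2-point reading is not attached to it.

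Three other stronger readings also fail.

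- **A success criterion.** The 2 points interpret a difference that is already significant. They did not drive the sample size and are not a decision rule for the trial.
- **A false-positive problem.** With no true difference, medians differ by 2 or more in 3.4–4.1% of simulated trials. The plan also requires significance, and with that condition the figure is about 1.5%.
- **Means at one visit and medians at another.** The article does not say that normality is judged visit by visit, so this is possible but not stated.

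The absence of a normality criterion or a fallback test is no finding: a condensed article may leave both to the analysis plan. The cited scores come from 12–24 months after CRFA, whereas this trial ends at 24 weeks, and no SD for NPRS after CRYO is given. The percentages are therefore illustrations.

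**Conclusion.** The point holds as a defect in a stated rule. If scores are judged non-normal, the plan as written replaces the between-arm difference and its CI with medians and IQRs, leaves the p-value mean-based, and does not say which summary is held against 2 points.

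For raw scores per arm, Shapiro-Wilk at 5%, 32 per arm and true shifts of 1.5–2.0, the branch would be triggered in roughly 30–72% of trials, and less often if change scores or residuals are checked. The case that matters most is a significant result, the switch triggered and the two summaries disagreeing about 2 points; it would arise in about 8–20%. These figures rest on the assumed shapes and normality check, and the disagreement is common only when the true shift is near 2.

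The documents do not support saying that the tests switch, that the trial's success turns on the 2 points, or that the type I error is materially inflated. The change is worth making before analysis because the ambiguity falls on the primary outcome and is easily removed.

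**What to change.** Replace the conditional reporting sentence for NPRS, KOOS and OKS with one fixed rule, for example:

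> The treatment effect is the baseline-adjusted between-arm difference in means from the planned model, reported with its 95% CI whatever the distribution of the scores. For NPRS, the 2-point MCID is read against this estimate and its CI. Medians with interquartile ranges are descriptive only.

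The planned ANCOVA already supplies this estimate. If skewness is a worry, add a bootstrap CI or a rank-based comparison as a sensitivity analysis.

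The cost is one sentence, with no change to the sample size, the visits or the data collected. The small downside is that a mean difference is reported for a skewed score; the medians can still be tabulated beside it.
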